### Sample size

2.4

This is a RCT with the BBR group as the intervention group and the placebo group as the control group. The 2-year DFS rate in postoperative CRC patients was set as the primary endpoint. According to our previous small-sample observations and literature review, the 2-year DFS rate was estimated to be 67% in the control group and 77% in the intervention group (4). A 1:1 parallel-group design was adopted, with a two-sided type I error α = 0.05 and a test power (1–β) = 0.8. Sample size calculation was performed using PASS 2021 software, yielding a required sample size of 316 patients in the intervention group and 316 patients in the control group. Considering a 15% dropout rate due to loss to follow-up and refusal, at least 363 patients were needed in each group, resulting in a total target sample size of 726 patients.

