### Statistical analysis

2.9

First, normality tests were performed on the measurement data. For data conforming to a normal distribution, parametric statistical methods including *t*-test, paired *t*-test, analysis of variance, and analysis of covariance were used. For non-normally distributed data, nonparametric methods such as rank-sum test and paired rank-sum test were adopted. Enumeration data were analyzed using chi-square test and Fisher's exact test, while ordinal data were analyzed using Ridit analysis, CMH test, or other nonparametric methods. In the multicenter comprehensive efficacy analysis, the CMH test was used for enumeration data, and analysis of covariance was used for measurement data. All statistical analyses were performed using SAS 9.3 software. For patients with missing data due to dropout or loss to follow-up, the last observation carried forward method may be used for imputation, followed by a sensitivity analysis of the results. All statistical tests were two-sided, and P < 0.05 was considered statistically significant.

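### The protocol permits LOCF for dropouts without exempting 2-year DFS; patients lost while disease-free would count as 2-year successes, with a bias whose size and direction depend on dropout by arm

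*Protocol article*

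**What the plan says.** Section 2.7.1 defines the primary endpoint as a proportion of enrolled patients by 2 years from randomization. Section 2.4 sizes it as a comparison of two proportions: "the 2-year DFS rate was estimated to be 67% in the control group and 77% in the intervention group".

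Section 2.9 lists tests by type of data. For counts it says "Enumeration data were analyzed using chi-square test", adds Fisher's exact test, and for the multicentre efficacy analysis says "the CMH test was used for enumeration data". On missing data it says: "For patients with missing data due to dropout or loss to follow-up, the last observation carried forward method may be used for imputation". The same sentence goes on to promise a sensitivity analysis, whose content is not given. DFS is neither named in that sentence nor excluded from it.

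Section 2.4 anticipates the loss: "Considering a 15% dropout rate due to loss to follow-up and refusal". Dropout is defined broadly. Section 2.3.4 includes withdrawal, loss to follow-up, serious adverse events, a pill count outside 80-120%, and chemotherapy for 3 months or less because of intolerance. Section 2.7.3 removes patients with grade 4 diarrhea from the study. Under section 2.7.2, status is assessed every 3 months for 2 years or until recurrence or metastasis.

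**The concern.** For an endpoint of the form event by 2 years, a patient who leaves before an event always has disease-free as the last observation. Carrying it forward to month 24 records a success, whether the patient left at month 3 or month 21. The imputation therefore errs in one direction within each arm, by an amount that grows with the number of dropouts and with how early they leave.

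Across arms, the errors cancel only if amount and timing of dropout match. Several of the protocol's dropout routes (tolerability, adherence, chemotherapy completion) could depend on the assigned treatment, so a match cannot be taken for granted. What is at stake is the type I error and the estimated effect on the primary endpoint. Because the wording only permits LOCF, it also leaves the handling of missing primary-endpoint data open to choice.

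**Working it through.** **Inputs from section 2.4.** DFS 67% (placebo) and 77% (berberine); "with a two-sided type I error α = 0.05 and a test power (1–β) = 0.8"; 1:1 allocation; 316 per arm before dropout; 15% dropout; 363 per arm after it.

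**Assumptions, not in the protocol.** The split of dropout by arm, its timing, and exponential event and dropout times, independent of each other.

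**Step 1: the plan's own figure.** Pooled two-proportion formula with mean proportion 0.72:

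n = [1.960·√(2·0.72·0.28) + 0.842·√(0.67·0.33 + 0.77·0.23)]² / 0.10² ≈ 315.3, rounded up to 316 per arm.

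This matches exactly. 316 × 1.15 = 363.4, the stated 363. Power is 80.1% at 316 and 85.2% at 363 with no dropout.

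**Step 2: what LOCF reports.** With true DFS S and dropout fraction d by 2 years, let λ = −ln(S)/2 and μ = −ln(1−d)/2. An event is seen only if it precedes dropout, so

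reported DFS = 1 − [λ/(λ+μ)]·[1 − S(1−d)].

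If all dropout happens at the start, reported DFS = d + (1−d)S.

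**Step 3: equal 15% dropout.**
- Placebo: λ = 0.2002, μ = 0.0813; 1 − 0.7113 × (1 − 0.67 × 0.85) = 69.4%.
- Berberine: λ = 0.1307; 1 − 0.6166 × (1 − 0.77 × 0.85) = 78.7%.
- The true 10 points read as 9.3. With all dropout at the start, 72.0% and 80.5% (rounded), a difference of 8.5.
- With no true effect the difference is 0.0 and type I error 5.0%.
- Power in simulation (4,000 trials, exponential dropout): LOCF 82.8%, Kaplan-Meier 83.5%.

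**Step 4: unequal dropout, no true effect (67% in both arms), 363 per arm.** Rejection rate of the pooled z test: Φ((δ − 1.96·SE₀)/SE₁) + Φ((−δ − 1.96·SE₀)/SE₁), where δ is the false difference and SE₀ and SE₁ are the pooled and unpooled standard errors. For dropout all at the start, δ = 0.33 × the difference in dropout.

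| Dropout, placebo vs berberine | Exponential: false difference, type I error | All at the start |
|---|---|---|
| 12.5% vs 17.5% | +0.8 points, 5.7% | +1.65 points, 7.8% |
| 10% vs 20% | +1.6 points, 7.7% | +3.3 points, 16.7% |
| 10% vs 25% | +2.5 points, 11.2% (11.9% simulated) | +4.95 points, 32.2% |

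Swapping the arms reverses the sign. The first two rows keep the planned 15% average; the third averages 17.5%. The abstract gives a total of 306 instead of 726; at 153 per arm the 10% vs 20% row gives 6.1% (exponential) or 9.8% (all at the start).

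**Step 5: unequal dropout, true 67% vs 77%, exponential.**
- 20% placebo, 10% berberine: 70.2% vs 78.1%, difference 7.9 points, power 68.4%.
- 10% placebo, 25% berberine: 68.6% vs 79.9%, difference 11.3 points.

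So LOCF can shrink or widen a true difference.

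**Step 6: censoring instead.** In simulation with no true effect, Kaplan-Meier at 24 months gives 0.0 points and 5.1% type I error at 10% vs 20%, and 0.0 points and 5.0% at 10% vs 25%. This holds because dropout was simulated as independent of recurrence.

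**The case against.** The best reply is that LOCF is only permitted, for missing data in general, with a sensitivity analysis to follow. Inflating 316 to 363 suggests that the planners were thinking of 316 evaluable patients, not of imputed ones. An unseen analysis plan may settle the matter, and a fixed 24-month proportion is consistent with the sizing. At equal 15% dropout the harm is small.

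Much of this stands. A reader might infer that LOCF is the declared primary analysis of DFS; the text does not say so. A reader might infer that type I error will be inflated, or that the result will favour berberine; that needs unequal dropout, for which the protocol gives no figure, and the direction could be either. A reader might infer that a true difference always shrinks; step 5 shows that it need not. Nor is the absence of Kaplan-Meier or log-rank a fault in itself in a condensed article.

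What does not stand is that the permission is harmless. It is the only missing-data method named, the primary endpoint is not exempted, and the sensitivity analysis has no content. An analysis plan that follows section 2.9 inherits the rule; one that censors instead has to depart from it.

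A second fair objection is aimed at the remedy. Section 2.3.4 itself says that short chemotherapy may raise the risk of recurrence, so some dropout is probably informative, and censoring would then be biased too. That is correct, and the fix allows for it.

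**Conclusion.** The point holds as a badly fixed rule: section 2.9 allows an imputation that is unsuitable for 2-year DFS and should exclude it. Under equal 15% dropout with exponential times, the cost is modest: about 2 points of overstatement in each arm, 9.3 instead of 10 points, no false effect and little loss of power relative to censoring. Under unequal dropout, which is an assumption, the false difference runs from about 0.8 to 2.5 points and type I error from about 5.7% to 11-12% over the splits shown, and more if dropout is early. The arm with more, or earlier, dropout looks better. All these figures assume dropout independent of recurrence; informative dropout would add bias that they do not capture.

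**What to change.** 1. In section 2.9, exclude DFS and recurrence from LOCF.
2. Make the primary analysis the difference in Kaplan-Meier 24-month DFS, with Greenwood standard error and 95% confidence interval, censoring at the last disease-free assessment. Event times are known only to the 3-monthly visit, so state the dating convention. Use log-rank or a centre-stratified Cox model as support.
3. Define the sensitivity analyses: dropouts counted as events, and a tipping-point analysis by arm.
4. State that recurrence and death data will still be used for patients labelled dropouts under sections 2.3.4 and 2.7.3, where obtainable from the scheduled visits or the telephone follow-up already provided for. This deals with informative dropout more directly than any censoring rule.

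The cost is protocol and analysis-plan wording, standard programming, and some continued outcome collection. The 67% versus 77% sizing basis is unchanged. As recruitment is under way, the change should be made before any unblinded look at outcome data.

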### Objectives

2.1

The primary objective is to evaluate the clinical efficacy and safety of BBR in preventing postoperative recurrence of stage IIIB/IIIC CRC. The secondary objectives are to elucidate the key mechanisms underlying BBR in preventing postoperative recurrence of CRC from the perspectives of gut microbiota and metabolism, screen biomarkers for the early and precise prediction of postoperative recurrence, and provide key targets for the prevention and treatment of CRC progression in the future.

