#### Secondary outcome measures

2.7.2

Secondary outcome measures include the 1-year and 2-year recurrence and metastasis rates, as well as the incidence of adverse events. Gut microbiome analysis will be performed using 16S rRNA gene sequencing to compare differences in gut microbial diversity and the abundance of characteristic genera between groups, and metabolomic analysis will be conducted to explore the correlation between serum and fecal metabolic profiles and clinical efficacy.

All assessments will be performed at baseline and every 3 months for 2 years following enrollment, or until disease recurrence or metastasis is observed in participants.

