## Discussion

3

Postoperative recurrence and distant metastasis remain a formidable clinical challenge in the management of CRC, particularly for patients with advanced-stage disease, in whom recurrence rates are markedly elevated and long-term prognosis is severely compromised. A previous RCT with long-term follow-up demonstrated that BBR may exert a potential preventive effect on colorectal adenoma postoperative recurrence, with its protective effect persisting for up to 6 years or even longer (25). Another study has shown that BBR can exert preventive and therapeutic effects on CRC by binding to SIGMAR1 (26). Building on these prior clinical findings, the present study specifically focuses on patients with stage IIIB and IIIC CRC. Through standardized intervention and long-term follow-up, we aim to further evaluate the preventive efficacy and potential of BBR against postoperative recurrence in this high-risk advanced CRC patient population.

Blood and fecal samples will be collected at baseline, 1-year treatment, 1-year follow-up or upon the occurrence of recurrence and metastasis for multi-omics analyses, specifically metagenomics (16S rRNA sequencing and shotgun metagenomics) and metabolomics (untargeted and targeted approaches). These samples will be used for comprehensive metabolic and mechanistic studies centered on gut microbiota-metabolite interactions and their roles in CRC recurrence.

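### Section 2.9 applies P < 0.05 to every test with no multiplicity control, which as written covers the microbiome and metabolomic screens

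*Protocol article*

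**What the plan says.** The Statistical analysis section (2.9) of the protocol article closes with a rule for all tests: "All statistical tests were two-sided, and P < 0.05 was considered statistically significant". Neither that section nor any other part of the article mentions family-wise or false-discovery control.

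The same article places high-dimensional screening among its stated aims:

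- Objectives (2.1): a secondary objective is to "screen biomarkers for the early and precise prediction of postoperative recurrence", alongside finding mechanisms and targets.
- Secondary outcome measures (2.7.2): 16S sequencing will be used to "compare differences in gut microbial diversity and the abundance of characteristic genera between groups". The section also plans to relate metabolite measurements in both sample types to treatment response.
- Discussion (3): shotgun sequencing is added to 16S, and the metabolomics is described as "metabolomics (untargeted and targeted approaches". On timing, "Blood and fecal samples will be collected at baseline, 1-year treatment, 1-year follow-up or upon the occurrence of recurrence and metastasis".

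The article does not say how many genera, metabolites or other features will be tested.

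**The concern.** A cut-off of 0.05 suits one confirmatory test, or a handful of clinical comparisons. Applied feature by feature across an omics platform, it admits a fixed 5% of all the features that do not differ, so the number of false hits grows with the size of the platform. Section 2.9 lists only single-variable methods (t-test, rank-sum, chi-square and the like), so testing each feature separately at 0.05 is the natural reading.

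At stake is how far the candidate biomarkers and targets can be trusted. Without error control, a reader of the results cannot tell which declared features are likely to be real. The trial's answer on disease-free survival does not depend on this.

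**Working it through.** **The plan's own figure.** The article gives no omics test count or error rate to reproduce. Its only computed figure at this alpha is the size for the primary endpoint, set "with a two-sided type I error α = 0.05 and a test power (1–β) = 0.8" with 67% versus 77%. With pooled variance:

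n = [1.960 × √(2 × 0.72 × 0.28) + 0.842 × √(0.67 × 0.33 + 0.77 × 0.23)]² / 0.10² ≈ 316 per arm.

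This matches the stated 316. The 0.05 level there is an ordinary level for one test, and that calculation is not in question.

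**Inputs for the omics screens.** From the article: threshold 0.05, two-sided, all tests. Assumed, because the article gives none: the number of features m, the share π that truly differ, and the power per feature.

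**Step 1: expected false positives per comparison when nothing differs, 0.05 × m.**

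- m = 20: 0.05 × 20 = 1
- m = 100: 5
- m = 1,000: 50
- m = 2,000: 100

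Correlation between features leaves these expected counts unchanged but makes the actual count more variable.

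**Step 2: chance of at least one false positive, 1 − 0.95^m, if tests are independent.** It is 64% at m = 20 and 99.4% at m = 100.

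**Step 3: several comparisons.** If 1,000 null metabolites were tested separately in serum and feces at the two scheduled post-baseline samplings, that is 2 × 2 = 4 comparisons and 4 × 50 = 200 expected false positives. This is an illustration; the article does not set out the comparisons.

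**Step 4: false share of the declared hits.** This does not depend on m:

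false share = 0.05(1 − π) / [0.05(1 − π) + power × π]

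For example, π = 5% at 80% power gives 0.0475 / (0.0475 + 0.0400) = 54%.

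| Share truly different | 80% power | 50% power |
|---|---|---|
| 1% | 86% | 91% |
| 2% | 75% | 83% |
| 5% | 54% | 66% |
| 10% | 36% | 47% |
| 20% | 20% | 29% |

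**Step 5: break-even.** False hits outnumber true ones when π < 0.05 / (0.05 + power):

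- 80% power: 0.05 / 0.85 = 5.9%
- 50% power: 0.05 / 0.55 = 9.1%
- 30% power: 0.05 / 0.35 = 14.3%

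**Step 6: effect of Benjamini-Hochberg at q = 0.05.** Simulation with 1,000 independent features, 80% unadjusted power per feature and 1,000 runs:

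| Share truly different | False hits, P < 0.05 | False hits, BH | True hits, BH | False share, BH |
|---|---|---|---|---|
| 1% (10 features) | 49 | 0.2 | 1.6 of 10 | about 5% |
| 5% (50 features) | 48 | 0.8 | 15 of 50 | about 5% |
| 10% (100 features) | 45 | 1.9 | 40 of 100 | about 4% |

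The unadjusted rule would find 80% of the true features in each row (8, 40 and 80), so the loss of yield is real.

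**The case against.** The strongest reply is that section 2.9 never says the P values are unadjusted. A 0.05 cut-off can be applied to adjusted P values. The section reads like a paragraph on clinical data and does not mention microbiome or metabolomics, and a journal article may leave the omics pipeline to an analysis plan that is not shown. Part of this stands: such a plan could add error control. But the sentence covers all tests, nothing in the article hints at adjustment, and the ordinary meaning of P < 0.05 is per test. The omics analyses are named as secondary outcomes, so the rule as written reaches them.

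Second, the article already uses partly exploratory language: it speaks of exploring a correlation and of screening. It limits the genus comparison to characteristic genera, which may be a short list, and the untargeted and shotgun methods appear only in the Discussion. This is fair and lowers the stakes. It does not remove them, because the Objectives also promise mechanisms and targets, and even 20 null features yield one expected false positive.

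Third, a reader might infer that the biomarker objective will return mainly false positives, or findings that chance alone produces. The article does not support that. It gives no feature count, true share or power, and at 80% power the false share is only 36% if 10% of features differ and 20% if 20% differ.

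Fourth, q < 0.05 is not the only defensible level for a screen. That stands; what matters is that a level is fixed in advance.

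**Conclusion.** The point holds in a limited form. As written, section 2.9 calls about 5% of truly null features significant in every omics comparison. Whether false hits form the majority depends on unknowns: they do if fewer than about 6% of features truly differ at 80% power per feature, or about 9% at 50% power, and they do not above those shares. Feature counts, true shares and per-feature power are all assumptions here; the 99.4% figure and the simulation also assume independent features.

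A reader might go further and take this as a flaw in the trial's main result. It is not: the primary disease-free survival test and its alpha are untouched. This is a correction the sponsor should make to the analysis rule, not a defect in design or conduct.

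**What to change.** Amend section 2.9 so that the unadjusted P < 0.05 rule applies only to the primary endpoint and the clinical secondary outcomes. For microbiome and metabolomic features, declare findings by the Benjamini-Hochberg false discovery rate at a prespecified level (for example q < 0.05) within each platform, sample type and contrast, and report them as exploratory candidates.

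This takes a sentence or two and no new patients, samples or data. Recruitment is under way according to the Trial status section, so the level should be fixed before any omics data are analysed. The cost is yield: in the illustration above, 1.6 of 10 true features are declared when 1% of features differ, and 15 of 50 when 5% do. If the sponsor finds that too strict for a screen, a more lenient q can be chosen, provided it is stated in advance.

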### Adverse events

2.10

All adverse events (including side effects such as gastrointestinal reactions and allergic reactions) will be documented in detail and graded throughout the study period. When a serious adverse event occurs, the investigators will provide all necessary treatment measures and report the adverse event to the Ethics Committee of the Second Affiliated Hospital of Zhejiang Chinese Medical University.

## Discussion

3

Postoperative recurrence and distant metastasis remain a formidable clinical challenge in the management of CRC, particularly for patients with advanced-stage disease, in whom recurrence rates are markedly elevated and long-term prognosis is severely compromised. A previous RCT with long-term follow-up demonstrated that BBR may exert a potential preventive effect on colorectal adenoma postoperative recurrence, with its protective effect persisting for up to 6 years or even longer (25). Another study has shown that BBR can exert preventive and therapeutic effects on CRC by binding to SIGMAR1 (26). Building on these prior clinical findings, the present study specifically focuses on patients with stage IIIB and IIIC CRC. Through standardized intervention and long-term follow-up, we aim to further evaluate the preventive efficacy and potential of BBR against postoperative recurrence in this high-risk advanced CRC patient population.

Blood and fecal samples will be collected at baseline, 1-year treatment, 1-year follow-up or upon the occurrence of recurrence and metastasis for multi-omics analyses, specifically metagenomics (16S rRNA sequencing and shotgun metagenomics) and metabolomics (untargeted and targeted approaches). These samples will be used for comprehensive metabolic and mechanistic studies centered on gut microbiota-metabolite interactions and their roles in CRC recurrence.

In recent years, accumulating evidence has underscored the pivotal role of gut microbiota dysbiosis in CRC initiation, progression, and recurrence (27). The gut microbiome and its metabolic products are now recognized as critical regulators of tumorigenesis, immune evasion, and therapeutic response in CRC patients. Specifically, CRC recurrence has been associated with distinct microbial signatures. On the one hand, enrichment of pathogenic oral pathobionts has been observed in CRC patients-Parvimonas micra, Fusobacterium nucleatum, and Peptostreptococcus stomatis were found to be significantly more abundant in tumors with microsatellite instability, forming a distinct bacterial network linked to colorectal carcinogenesis (28). On the other hand, depletion of beneficial commensals is also a hallmark of CRC-associated dysbiosis. Faecalibacterium prausnitzii and Akkermansia muciniphila are recognized as next-generation probiotics with anti-inflammatory and barrier-protective properties, and their reduced abundance has been documented in CRC patients (29). These microbial alterations contribute to a pro-tumorigenic microenvironment by promoting chronic inflammation, producing genotoxins (e.g., colibactin), and disrupting bile acid metabolism (26). Complementing gut microbiome research, metabolomics has emerged as a powerful tool for investigating CRC recurrence mechanisms and identifying non-invasive biomarkers. Gut microbial metabolites, including short-chain fatty acids (SCFAs), bile acids, tryptophan derivatives, and polyamines, play role in CRC recurrence: they can serve as early warning indicators for disease progression (30).

The potential molecular mechanism by which BBR prevents postoperative recurrence of CRC can be comprehensively explored through integrated gut microbiota and metabolomics analyses. Previous studies have confirmed that BBR exerts its anti-tumor effects by: (1) reshaping gut microbiota composition, which is manifested by increasing the Bacteroidetes/Firmicutes ratio in most CRC models and clinical studies, promoting the enrichment of SCFA-producing bacteria (e.g., Faecalibacterium and Roseburia), and inhibiting the proliferation of pathogenic species such as Fusobacterium nucleatum (31, 32); (2) modulating systemic bile acid homeostasis in a dose-dependent manner, and suppressing the accumulation of tumor-promoting secondary bile acids, including deoxycholate (33); (3) triggering GPX4-dependent ferroptosis and impairing mitochondrial energy metabolism (34); (4) regulating key signaling pathways involved in tumor progression (e.g., Wnt/β-catenin and NF-κB) (16, 35). These findings provide an important foundation for our integrated metagenomics and metabolomics approach to unravel the core mechanisms underlying BBR's anti-recurrence effects.

This study is a multicenter, double-blind RCT with high-level evidence and strong reliability. It aims to explore a feasible therapeutic regimen for the prevention of postoperative recurrence of CRC.

Despite the potential geographical limitation of our enrolled participants, who are predominantly from the eastern coastal regions of China, this multicenter, double-blind RCT still provides high-level evidence to support the preventive efficacy of BBR against CRC postoperative recurrence. More importantly, our study is designed to elucidate the core mechanistic pathways by which BBR exerts its anti-recurrence effects, including the modulation of gut microbiota-metabolite crosstalk and the regulation of key signaling pathways involved in tumor metastasis. These findings will not only enrich the theoretical basis for BBR application in CRC clinical management but also provide novel strategies and actionable targets for the development of targeted preventive interventions for advanced CRC patients. Collectively, this study holds significant clinical translational value, aiming to optimize the postoperative recurrence prevention strategy for CRC and improve the long-term survival and quality of life of patients.

